## Abstract

**Introduction:**

The growing number of adolescents and young adults (AYAs) living with chronic conditions highlights the need for effective healthcare transition programmes (TPs) to support the transfer from paediatric to adult care. Despite existing recommendations, many AYAs experience inadequate preparation, resulting in disrupted care and adverse health outcomes. The COCCOS project developed a co-designed TP to address these challenges. This study presents the protocol for an evaluation of this programme.

**Methods and analysis:**

A multicentric quasi-experimental pretest–posttest study will be conducted in two Belgian university hospitals. AYAs aged 17–18 years with type 1 diabetes, asthma, or obesity will be recruited into an intervention group receiving the COCCOS TP or a control group receiving usual care. The intervention consists of four structured consultations over 13–16 months, focusing on transition preparation, autonomy, and continuity of care. Primary outcome is transition readiness, measured using the Transition Readiness Assessment Questionnaire. Secondary outcomes include patient empowerment, medication adherence, health-related quality of life, and mental health. Data will be collected at baseline, transfer, and four months post-transfer. Cost-effectiveness will be assessed from a healthcare payer perspective using quality-adjusted life years. A mixed-methods process evaluation will examine implementation fidelity, acceptability, and contextual factors through observations, surveys, and interviews. The study is registered on ClinicalTrials.gov under identifier NCT07145671.

**Discussion and conclusion:**

This study will provide comprehensive evidence on the feasibility, preliminary effectiveness, cost-effectiveness, and implementation of a co-designed TP in real-world clinical practice. By integrating clinical, economic, and process outcomes, it addresses key gaps in transitional care research. Findings will inform refinement of the programme and the design of a future large-scale trial, contributing to the development of sustainable, patient-centred transition care for AYAs with chronic conditions.

## 1. Introduction

The rising prevalence of chronic conditions poses a growing challenge to health systems worldwide. Over the past decade, the number of adolescent and young adults (AYAs) living with a chronic condition has grown, with an estimated 10–25% affected, of whom over 85% have the prospect of surviving into adulthood [1–3]. This shift is driven by both an increasing prevalence of childhood-onset conditions, such as asthma, obesity, and type 1 diabetes, associated with environmental, behavioural, and diagnostic factors, as well as improved survival rates among children with congenital conditions, including cystic fibrosis and congenital heart disease [3].

Despite improved survival rates, these individuals often continue to carry a lifelong disease burden and an increased risk of complications, requiring continuous and specialized care across the life course [4,5]. Given that healthcare needs change considerably across the lifespan, AYAs are required to transition from paediatric to adult-oriented care upon reaching adulthood [4,5]. This process requires timely developmental and practical preparation, yet many patients transfer before being adequately prepared [4,5]. Indeed, approximately half of AYAs and their families do not receive sufficient support for this transfer [6]. Adolescence is a particularly vulnerable period, characterized by psychosocial and physical changes that may reduce treatment adherence and increase risk-taking behaviours [7,8]. As a result, up to 40% of AYAs experience disrupted care after transfer to adult services [9,10], often due to differences in care organization, including reduced interdisciplinary support, greater emphasis on patient autonomy, and limited expertise in childhood-onset conditions and the specific needs of young adults [11]. Such disruptions may lead to adverse outcomes such as worsening health status, treatment non-adherence, discontinuation of care, increased hospitalizations and emergency department visits, and higher healthcare costs [12–15].

Structured healthcare transition programmes (TPs) are, therefore, recommended to support a gradual and well-prepared transition towards adulthood and adult care. By fostering self-management skills, improving treatment adherence, and empowering patients, TPs aim to prevent health deterioration and may reduce healthcare costs by 3–14% [16]. Although several guidelines highlight the importance of transitional care, important knowledge gaps in real-world data and effectiveness remain [5,14], particularly regarding which programme elements are most beneficial in specific contexts and populations, process-level factors such as uptake and implementation, and experiences of patients and caregivers [15,17]. Recent consensus statements from the American and European paediatric societies call for more research, especially on common conditions like asthma and childhood obesity [14,18]. While empirical data support the clinical effectiveness of TPs, their long-term sustainability within everyday routine hospital care pathways remains limited [19].

Building on the first work package of the COCCOS project, which developed a TP using an experience-based co-design (EBCD) methodology [20,21], this study presents the protocol for the second phase: a multicentric quasi-experimental study. The study aims to provide insights into the program’s potential impact on clinical and patient-reported outcomes, its cost-effectiveness, and the experiences of patients and healthcare providers with its implementation.

## 2. Methods

### 2.1. Study design

A multicentric quasi-experimental pretest-posttest study was designed to evaluate a healthcare transition programme in AYAs with chronic conditions. This design enables the assessment of outcomes over time within an intervention cohort, while also allowing comparison with a cohort receiving standard care. The quasi-experimental approach was selected to account for the practical constraints of real-world clinical settings, where randomization is often neither feasible nor appropriate, including limitations related to time investment for patients and healthcare providers, potential burden of repeated measurements, reduced feasibility of frequent follow-up in the control group, and an increased risk of attrition in a fully randomized design. In addition to evaluating effectiveness, this design supports the assessment of implementation processes and the experiences of both patients and healthcare providers, thereby providing a comprehensive evaluation of the intervention in routine care practice in Flanders (Belgium). At the time of manuscript submission, the study is ongoing. Participant recruitment took place between March 2025 and March 2026. Data collection will continue until December 2026, allowing for follow-up of enrolled participants according to the study protocol. Data analysis is anticipated to be completed by March 2027, with study results expected to be reported in 2027. The study is registered on ClinicalTrials.gov under identifier NCT07145671. More details can be found at: https://clinicaltrials.gov/study/NCT07145671?cond=Coccos&viewType=Card&rank=1.

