**Fig 1 pone.0353932.g001:**
[figure not shown]
SPIRIT checklist.

In brief, the TP consists of four key components delivered over a period of 12–16 months, depending on pathology-specific care trajectories (see Fig 2):

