**Fig 2 pone.0353932.g002:**
[figure not shown]
Overview of the four key moments in the COCCOS transition programme.

(1) **Key moment 1: Introducing healthcare transition *“Hey there!”* (17 years):** This initial, paediatric care-led consultation introduces the concept and trajectory of healthcare transition to the AYA and their family. The timing of transfer to adult care is determined through shared decision-making. A paediatric healthcare provider is appointed as the primary contact person – preferably someone already trusted by the AYA – and can be contacted for any transition-related concerns. In addition, AYAs are encouraged to identify a contact person within their personal support network. All agreements and relevant information are documented in an individualized transition plan. AYAs receive brochures and flyers containing information on healthcare transition, including what the transition entails, the key differences between paediatric and adult care services, and details about their future adult-care team.(2) **Key moment 2: Split visit *“Almost ready?”* (17.5 years):** At least one independent consultation takes place between the introductory and joint consultation. During this visit, parents or family members may be asked to leave part of the consultation to encourage autonomy and direct communication between the AYA and the healthcare provider. Prior to the consultation, AYAs are asked to complete the Ready Steady Go checklist [23], which serves as a structured tool to assess transition readiness. The individualized transition plan is reviewed and updated accordingly, and any concerns raised by the AYA are addressed by the paediatric team.(3) **Key moment 3: Joint consultation *“Almost there!”* (18 years):** The final consultation before transfer is conducted jointly by paediatric and adult healthcare providers. This consultation facilitates continuity of care and allows the AYA to become acquainted with the adult care team. A contact person within the adult care setting is appointed. The Ready Steady Go-checklist is completed beforehand to guide the consultation and ensure that key transition domains are addressed.(4) **Key moment 4: Feedback moment *“Tell us your story!*” (18.5 years):** Approximately three to four months after transfer, preferably after the first adult care consultation, the COCCOS researcher contacts the AYA to evaluate the transition process. The Ready Steady Go-checklist is completed beforehand to support reflection. Feedback is communicated to both paediatric and adult care teams, and any arising issues are addressed through additional support, referrals, or extra consultations if needed.

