### 2.3. Setting, participants, and recruitment

#### 2.3.1. Setting.

The study will be conducted at the Queen Mathilde Mother and Child Center, Antwerp University Hospital (UZA), and the Princess Elisabeth Pediatric Hospital, University Hospital Ghent (UZ Ghent). The TP will be implemented over a total period of 16 months, including a post-transfer assessment (see Fig 3).

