**Fig 3 pone.0353932.g003:**
[figure not shown]
Overview of the quasi-experimental pre-test post-test study.

Participants in the intervention group will receive the TP over 13–16 months, depending on the trajectory specific to their condition. Questionnaire assessments will be administered at three time points: at baseline, prior to the start of the intervention (T0); at the time of transfer to adult care services (T1), with the questionnaire completed immediately after the last consultation on paediatric care services; and four months post-transfer (T2). For the control group, whom receive usual care, assessments will be conducted at the time of transfer (T1), with the questionnaire completed immediately after the last consultation on paediatric care services, and four months post-transfer (T2).

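### Data collection to December 2026 does not allow T2 for intervention participants enrolled after about August to November 2025, yet recruitment is said to run to March 2026

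*Protocol article*

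**What the plan says.** Section 2.1 fixes the calendar. On enrolment: "Participant recruitment took place between March 2025 and March 2026". On follow-up: "Data collection will continue until December 2026, allowing for follow-up of enrolled participants according to the study protocol". On reporting: "Data analysis is anticipated to be completed by March 2027". The recruitment window is pooled; no dates are given by group.

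The programme length appears in several places:

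- Section 2.3.1, text under Fig 3 (the Abstract gives the same range): "Participants in the intervention group will receive the TP over 13–16 months, depending on the trajectory specific to their condition".
- Section 2.3.1, first paragraph: "The TP will be implemented over a total period of 16 months, including a post-transfer assessment".
- Section 2.2, text under Fig 1: "four key components delivered over a period of 12–16 months".

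Section 2.3.1 places T0 before the programme starts, T1 at transfer and T2 four months after transfer. The last programme component, key moment 4 in section 2.2, comes "Approximately three to four months after transfer", so the programme ends at T2 or slightly before it. Section 2.3.2 admits intervention participants aged 17 whose transfer is planned within 12 months. Controls are aged 17.5–18, have transfer planned in the near term, and have only T1 and T2.

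**The concern.** Only nine months lie between the end of recruitment and the end of data collection, while the intervention group needs 13–16 months from T0 to T2. The statement that the end date allows follow-up according to the protocol therefore cannot hold for an intervention participant enrolled late in the window.

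Three things are at stake. First, intervention T2 data would come from early enrolees or unusually fast transfers, which adds a selection mechanism to a design that already allocates by age (section 2.3.3). Second, T2 supplies the post-transfer comparison and part of the EQ-5D-5L input to the economic model. Third, section 3 offers retention as a key parameter for a future larger study. If late enrolees whose T2 falls after the closing date are counted as lost, retention will look worse than it was.

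**Working it through.** **Inputs.** Recruitment March 2025 to March 2026, data collection to December 2026 and analysis complete by March 2027 (section 2.1). Programme 13–16 months (section 2.3.1), with a 12–16 month variant (section 2.2). At least 28 recruits and 22 required per group (section 2.3.2). December 2026 is read as 31 December, the most favourable reading. The article does not state the accrual pattern; uniform accrual is assumed where a share is given.

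**Step 1: does the stated end date cover the last enrolee?** Date of T2 = enrolment date + time from T0 to T2.

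- 31 March 2026 + 12 months = 31 March 2027
- 31 March 2026 + 13 months = 30 April 2027
- 31 March 2026 + 16 months = 31 July 2027

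The December 2026 date is not reproduced under any stated duration. On 13–16 months, T2 also falls after the analysis is due to be complete. To fit, someone enrolled on 31 March 2026 would have to transfer within 9 − 4 = 5 months of entry, giving T2 at 9 months, which is shorter than any programme length stated.

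**Step 2: last workable enrolment date** = 31 December 2026 − time to T2.

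- 12 months: 31 December 2025
- 13 months: 30 November 2025
- 16 months: 31 August 2025

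**Step 3: share enrolled too late, if accrual was uniform** = days in the window after the last workable date ÷ days in the window.

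| Recruitment window | 12 months | 13 months | 16 months |
|---|---|---|---|
| 1 Mar 2025 to 31 Mar 2026 (396 days) | 90/396 = 22.7% | 121/396 = 30.6% | 212/396 = 53.5% |
| 1 Mar 2025 to 1 Mar 2026 (366 days) | 60/366 = 16.4% | 91/366 = 24.9% | 182/366 = 49.7% |
| 31 Mar 2025 to 31 Mar 2026 (366 days) | 90/366 = 24.6% | 121/366 = 33.1% | 212/366 = 57.9% |

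In whole months the first row gives 4/13 = 31% and 7/13 = 54%. If data collection closed on 1 December instead, the first row would be 38% (13 months) to 61% (16 months).

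**Step 4: numbers, full window, before any dropout.**

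- 13 months: 28 × (1 − 0.306) = 19.4
- 16 months: 28 × (1 − 0.535) = 13.0

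So about 13–19 of 28 could reach T2.

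**Step 5: T1.** Transfer is four months before T2, so T1 falls 9–12 months after entry. At 9 months, everyone enrolled by 31 March 2026 reaches T1 by 31 December 2026. At 12 months, (396 − 90)/396 = 77% do. T1 is far less exposed than T2.

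**Step 6: controls.** A control aged 17.5 enrolled in March 2026 who transfers at 18, in about September 2026, reaches T2 in about January 2027. Most controls, with transfer in the near term, should fit the calendar, but the latest may not.

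**The case against.** The strongest reply is that the window is pooled. If intervention enrolment closed by August to November 2025 and later recruits were all controls, every date in section 2.1 could stand. Recruitment is reported in the past tense, so the authors presumably know the actual dates, and Figs 2 and 3 are not visible here. This stands as a limit on the size of the problem: the loss could be near zero. It does not rescue the text, because the article states no earlier closing date and makes its claim about follow-up for enrolled participants generally.

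It is also fair that between-group comparisons are described as primarily descriptive and exploratory, and that section 2.5.1 promises transparent handling of missing data. That softens the consequences, but it does not make the dates agree or separate administrative truncation from dropout.

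A reader might infer stronger conclusions that the document does not support:

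- **That a third to a half of the intervention group will lack T2.** This holds only under uniform accrual to the end of March 2026 on a 13–16 month programme.
- **That truncation and attrition together leave far fewer than 22.** The 25% attrition rate is stated for 24 months, so applying it in full on top of truncation over 13–16 months overstates the loss. The 22 per group is not tied to T2. Moreover, 28 × 0.75 = 21 is already below 22 without truncation, which is a separate sample-size matter.
- **That the control group will be nearly complete.** The near term is not defined, and step 6 shows that a late control can miss T2.
- **That the nominal ages at the key moments (17 to 18.5 years) prove an 18-month programme.** The same text puts the last moment three to four months after transfer, so 18.5 reads as rounding.

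**Conclusion.** The concern holds as a conflict of dates. On the stated programme length, an intervention participant enrolled after about 30 November 2025 cannot reach T2 by the end of December 2026, and the article gives no earlier closing date for that group. This needs no accrual assumption beyond at least one intervention enrolment after the cut-off.

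The size is conditional. With uniform intervention accrual from 1 March 2025 to 31 March 2026, about 31–54% would miss T2. With a 12-month window ending 1 March 2026 it is 25–50%. With a 12-month programme it is 16–25%, depending on the window. Front-loaded enrolment or early transfers would lower all of these. The effect falls mainly, not solely, on the intervention group, and mainly on T2. The statement in section 2.1 should not stand as written.

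**What to change.** 1. In section 2.1, state first and last enrolment dates separately for the intervention and control groups, and say whether all T2 assessments fall within data collection.
2. Reconcile the programme durations (12–16, 13–16 and 16 months), and say whether each includes T2.
3. If any intervention participant enrolled too late, choose one of two courses:
   - Extend T2 collection to the last enrolee's T2 (up to July 2027) and move the analysis date to match.
   - Keep the end date, state that T2 is administratively censored for late enrolees, give the expected T2 number, and report it separately from dropout in the retention figures and T2 results. Treat late controls in the same way.

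**Cost.** The first two items are wording only. Extending means up to seven more months of follow-up (December 2026 to July 2027) and a later report; the questionnaires already go out by automated email. Declaring censoring costs only wording and an openly smaller T2 sample. The choice should be made before December 2026, because T2 data not collected on time cannot be recovered. Making T1 the main time point or using a repeated-measures model are options, but this point does not require them.

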### 2.2. COCCOS transition programme

The TP was developed within the first work package of the COCCOS project, in close collaboration with key stakeholders, including AYAs, parents, and healthcare providers. A participatory action research approach was adopted, incorporating methods such as EBCD and photovoice [20,22]. Detailed information on the development and content of the TP has been described previously [21]. Fig 1 presents the SPIRIT checklist for this research.

**Fig 1 pone.0353932.g001:**
[figure not shown]
SPIRIT checklist.

In brief, the TP consists of four key components delivered over a period of 12–16 months, depending on pathology-specific care trajectories (see Fig 2):

**Fig 2 pone.0353932.g002:**
[figure not shown]
Overview of the four key moments in the COCCOS transition programme.

(1) **Key moment 1: Introducing healthcare transition *“Hey there!”* (17 years):** This initial, paediatric care-led consultation introduces the concept and trajectory of healthcare transition to the AYA and their family. The timing of transfer to adult care is determined through shared decision-making. A paediatric healthcare provider is appointed as the primary contact person – preferably someone already trusted by the AYA – and can be contacted for any transition-related concerns. In addition, AYAs are encouraged to identify a contact person within their personal support network. All agreements and relevant information are documented in an individualized transition plan. AYAs receive brochures and flyers containing information on healthcare transition, including what the transition entails, the key differences between paediatric and adult care services, and details about their future adult-care team.(2) **Key moment 2: Split visit *“Almost ready?”* (17.5 years):** At least one independent consultation takes place between the introductory and joint consultation. During this visit, parents or family members may be asked to leave part of the consultation to encourage autonomy and direct communication between the AYA and the healthcare provider. Prior to the consultation, AYAs are asked to complete the Ready Steady Go checklist [23], which serves as a structured tool to assess transition readiness. The individualized transition plan is reviewed and updated accordingly, and any concerns raised by the AYA are addressed by the paediatric team.(3) **Key moment 3: Joint consultation *“Almost there!”* (18 years):** The final consultation before transfer is conducted jointly by paediatric and adult healthcare providers. This consultation facilitates continuity of care and allows the AYA to become acquainted with the adult care team. A contact person within the adult care setting is appointed. The Ready Steady Go-checklist is completed beforehand to guide the consultation and ensure that key transition domains are addressed.(4) **Key moment 4: Feedback moment *“Tell us your story!*” (18.5 years):** Approximately three to four months after transfer, preferably after the first adult care consultation, the COCCOS researcher contacts the AYA to evaluate the transition process. The Ready Steady Go-checklist is completed beforehand to support reflection. Feedback is communicated to both paediatric and adult care teams, and any arising issues are addressed through additional support, referrals, or extra consultations if needed.

The intervention will be delivered during routine outpatient consultations with the paediatrician, supported by structured guidance from the research team, including preparatory contact before each consultation. Its design and delivery are based on insights from the EBCD process, which highlighted the need for clear structure, consistency across providers, and practical tools to support transition discussions. Prior to each consultation, the paediatrician will be contacted by the researcher and informed about the specific component of the intervention to be delivered at that visit, ensuring timely preparation and alignment with the study protocol.

To facilitate implementation, the research team will provide a paper folder containing all intervention materials, including the Ready Steady Go-checklists, the individualized transition plan, and informative brochures and flyers. The folder is organized in a stepwise manner, corresponding to the sequence of consultations, and includes a checklist with concrete action points for each visit. These checklists specify the key elements to be addressed, such as topics to discuss, documents to complete, and actions to be taken with the adolescent and their family. These standardised implementation tools support the paediatrician in delivering the intervention as intended, while reducing variability between providers and centres. In addition, the use of standardized materials and checklists promotes intervention fidelity and completeness, while still allowing flexibility to tailor discussions to the individual needs of the adolescent. The integration of the intervention into routine consultations minimizes additional burden on both patients and healthcare providers, thereby enhancing feasibility and facilitating potential future implementation in standard care.

